### Dissemination Plan

The findings of this study will be disseminated through open-access, peer-reviewed publications and presentations at clinical and scientific meetings. This protocol represents the first of 2 planned manuscripts. The main results paper is anticipated for submission in the first half of 2026. Upon publication of the results, raw sequencing data (FASTQ files) will be deposited in the European Nucleotide Archive. The bioinformatic workflow (Python/QIIME 2 scripts) will be made available in a version-controlled repository or provided upon reasonable request to support transparency and reproducibility. Pseudonymized metadata will be shared with qualified researchers upon request in compliance with GDPR and institutional requirements.

Interested participants may request a plain-language summary of the study results in German. Study registration in DRKS/WHO ICTRP ensures continuous transparency, and future updates to the study outputs will be linked to the registry entry. The decentralized design and methodological framework developed here are intended to inform larger maternal health studies and may be adapted for broader applications in remote microbiome research.

## Results

The recruitment and sample collection phase of the study has been completed. Between May 2022 and October 2023, a total of 37 participants were enrolled, including 25 women in the CS group and 12 in the VD group. Recruitment concluded below the originally planned sample size, reflecting real-world constraints in this peripartum population. Follow-up was completed with receipt of the final stool sample in March 2024. An overview of baseline characteristics of participants who returned at least one stool sample is presented in Table 1. DNA extraction and 16S rRNA gene sequencing were completed in a single batch in October 2024. All samples passed quality control and were retained for downstream analyses. An overview of included and excluded samples by group and time point is provided in Figure 2. Bioinformatic processing and statistical analyses were initiated in June 2025 and were ongoing as of December 2025.

**Table 1. T1:** Baseline characteristics of participants who submitted at least 1 sample (N=31)^a^.

Characteristic		Total (N=31)	CS^b^ with PAP^c^ (n=20)		VD^d^ without PAP (n=11)	
Continuous variables						
Age (y), median (IQR)		37 (33-39)	37 (33-39)		36 (33-38)	
Categorical variables, n (**%**)						
Delivery mode						
CS		20 (65)	20 (100)		—^e^	
VD		11 (35)	—		11 (100)	
Multiple births						
Yes		2 (6)	2 (10)		0 (0)	
No		29 (94)	18 (90)		11 (100)	
Parity						
0		12 (39)	9 (45)		3 (27)	
1		13 (42)	5 (25)		8 (73)	
2		5 (16)	5 (25)		0 (0)	
3		0 (0)	0 (0)		0 (0)	
4		0 (0)	0 (0)		0 (0)	
5		1 (3)	1 (5)		0 (0)	
>1		19 (61)	11 (55)		8 (73)	

a Only participants in the CS group received PAP; no antibiotics were administered in the VD group.

b CS: cesarean section.

c PAP: perioperative antibiotic prophylaxis.

d VD: vaginal delivery.

e Not applicable.

**Figure 2. F2:**
[figure not shown]
Flowchart of participant enrollment, allocation, follow-up, and analysis in the MAMA (Microbiome Changes Due to Antibiotic Prophylaxis in Mothers at Birth) study, in line with the STROBE (Strengthening the Reporting of Observational Studies in Epidemiology) recommendations for observational studies. CS: cesarean section; VD: vaginal delivery.

A per-protocol sample was defined as a stool sample received within the prespecified time window and passing quality control. Protocol deviation was defined as exclusion from the per protocol set due to intake of antimicrobial agents (antibiotic or antifungal) other than the study medication or as sample collection outside the defined protocol windows and could not be assigned to a valid time point. Two women, who were initially allocated to the vaginal delivery group, delivered by CS and were therefore analyzed in the CS group; these women are counted under vaginal delivery at baseline (T0) and under CS at follow-up (T1 and T2). Numbers reported per group reflect participants analyzed at each time point; totals across groups were: T0 (n=31), T1 (n=19), T2 (n=21), and final analysis (N=71).

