**Methods:**

The MAMA (Microbiome Changes Due to Antibiotic Prophylaxis in Mothers at Birth) study is a prospective, 2-arm observational cohort study conducted entirely off-site. Women in the third trimester of pregnancy were recruited at 2 German level-1 perinatal centers and affiliated outpatient facilities. Participants underwent either CS with PAP (single dose cefuroxime 1.5 g intravenously) or VD without antibiotics. Stool samples were self-collected at home and returned by mail at 3 predefined time points: late pregnancy (T0), 2 to 3 days post partum (T1), and 90±10 days post partum (T2). Primary outcomes are feasibility indicators, including recruitment rate, sample and questionnaire return rates at each time point, adherence to sampling windows, and participant retention across follow-up. Secondary outcomes are exploratory microbiome measures based on 16S rRNA gene sequencing (V3-V4), including alpha diversity indices, beta diversity metrics, and relative taxonomic abundances. Microbiome analyses are explicitly compositional and hypothesis-generating. Group comparisons and longitudinal within-individual changes will be assessed using nonparametric diversity metrics and multivariate distance–based methods. No confirmatory hypothesis testing is planned.

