The study was explicitly implemented as a fully remote, decentralized design to minimize participant burden during pregnancy and early postpartum. All study procedures, including screening, informed consent, questionnaire completion, and stool sampling time points, were completed by participants at home. Communication occurred via telephone or institutional email. Preassembled sampling kits were mailed to participants and included written instructions, a stool catcher, a DNA stabilization tube enabling reliable sample quality even when samples remained at home for several days before mailing, a structured paper–based metadata questionnaire, and a preaddressed return envelope. Participants received reminder notifications from the study coordinator regarding upcoming collection time points and missing documentation. The absence of mandatory on-site visits enabled flexible participation, allowing women to complete all study tasks according to their individual schedules and daily responsibilities. This design facilitated nationwide participation and broadened accessibility, particularly for individuals living in rural areas, with limited mobility, or with substantial childcare and occupational commitments.

The study was developed and implemented in close collaboration between microbiologists, clinical pharmacists, obstetricians, and allied health care professionals, ensuring both methodological rigor and practical feasibility. The reporting of this protocol follows the STROBE (Strengthening the Reporting of Observational Studies in Epidemiology) recommendations (Checklist 1) for observational cohort studies, as recommended by the EQUATOR Network [24].

The study was registered in the German Clinical Trials Register (DRKS00027305), which is part of the WHO International Clinical Trials Registry Platform (ICTRP).

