### Data Collection and Sample Handling

Sample collection was performed independently by participants at home as part of the fully remote study workflow. Final group assignment (CS vs VD) was based retrospectively on the actual mode of delivery at birth. Each participant was asked to provide 3 stool samples at predefined time points: during late pregnancy (T0, from gestational week 32 onward), within 2 to 3 days postpartum (T1), and at 90 (±10) days postpartum (T2). These time points were selected to capture baseline microbiome composition, immediate peripartum changes, and long-term recolonization dynamics. For each time point, participants received a sample collection kit that included a collection tube (DNA/RNA Shield Fecal Collection Tube, Zymo Research), a single-use stool catcher (Feces Catcher, Zymo Research), written instructions, and a prepaid return envelope. Paper-based questionnaires accompanied each sample kit and covered maternal health status, medication use, pregnancy and birth-related variables, and lifestyle factors such as nutrition and physical activity. Participants returned both the stool sample and completed questionnaire in the same shipment. Questionnaires were designed to be completed within approximately 10 minutes and spanned 2 to 3 pages, depending on the time point. Incomplete or missing forms were actively followed up by the study coordinator.

Samples were shipped by standard postal service and received by the coordinating study center. Although the exact time between sampling and mailing was not recorded for all participants, no sample exceeded the manufacturer’s recommended stability window.

Upon arrival, samples were documented and immediately stored in a temperature-monitored, alarm-secured refrigerator at 4°C to 8 °C, where they remained until DNA extraction. The median storage duration was 434 days (range: 137‐784 d), with no deviations from the defined storage conditions. Despite the stabilizing effect of DNA/RNA Shield, the wide range of storage periods may still cause subtle bias.

The nucleic acid stabilization buffer (DNA/RNA Shield) ensures preservation of microbial DNA for at least 24 months at ambient temperature (4° C‐25  °C) and indefinite stability when frozen (<−20 °C), according to the manufacturer. Accordingly, all returned samples were accepted for processing. No exclusions were made due to transport delays, damage, or temperature fluctuations.

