### Outcomes

The primary outcomes of this protocol are feasibility indicators that assess the performance of the fully remote study design. These include the proportion of contacted women who enrolled; sample and questionnaire return rates at T0, T1, and T2; timeliness of sample returns relative to the predefined sampling windows; and overall participant retention across study time points. Together, these measures evaluate compliance, protocol adherence, and the suitability and scalability of the decentralized workflow for maternal microbiome research.

Microbiome-related outcomes are exploratory and focus on compositional rather than absolute changes in microbial communities, as 16S rRNA-sequencing yields relative abundances. These outcomes include alpha diversity metrics (eg, Shannon index and Chao1 richness), beta diversity metrics (eg, Bray-Curtis dissimilarity, and weighted and unweighted UniFrac distances), and relative abundances of bacterial taxa across taxonomic levels from phylum to genus with ASV-level feature tables used for technical analyses. Exploratory identification of marker taxa may be performed where feasible. No diagnostic or clinical interpretations of “dysbiosis” will be drawn.

In line with the observational design and modest, imbalanced sample size, all hypotheses are nonconfirmatory and serve to guide hypothesis-generating analyses. We hypothesize that women undergoing CS with PAP will exhibit a transient reduction in alpha diversity at T1 compared to VD; that compositional perturbations at T1 will at least partially resolve by T2; and that the relative abundance of *Clostridioides difficile* will be higher at T1 in the CS group than in VD. These hypotheses reflect biologically plausible patterns without implying confirmatory testing.

Exploratory analyses will consider associations between microbiome features and maternal metadata such as parity, medication intake, and dietary patterns, where feasible. Subgroup analyses may be limited by sample size constraints, and residual confounding is expected.

Outcomes will be described both cross-sectionally (CS vs VD at each time point) and longitudinally (across T0→T1→T2 within individuals as well as within groups). The statistical procedures for these analyses are outlined in the subsequent section.

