### Statistical Analysis Plan

The following procedures specify how the predefined outcomes will be analyzed. The analysis will follow an exploratory framework. Although simple, biologically plausible hypotheses have been specified, no formal power calculation was performed. Consequently, results will be interpreted as hypothesis-generating rather than confirmatory.

Feasibility outcomes will be summarized descriptively using proportions, medians, and ranges. Timing of sample returns relative to the predefined collection windows (T0, T1, and T2) will be evaluated by calculating time intervals (in d) between the target and actual return dates. These intervals will be summarized using medians and IQR and compared between delivery groups where appropriate. Reasons for loss to follow-up (eg, no sample returned) will be documented, and analyses will be performed on available cases without imputation of missing data. This analysis will help assess protocol adherence and identify potential logistical barriers in the home-based study model.

To address the previously defined microbiome outcomes, the following statistical approaches will be applied: group comparisons between CS and VD will be performed for each time point (T0, T1, and T2) and longitudinally within participants as well as within groups, using all available paired samples (eg, T0-T1 or T1-T2), where applicable. Alpha diversity metrics (eg, Shannon index and Chao1 richness) will be compared using nonparametric tests (Wilcoxon rank-sum or Kruskal-Wallis test). Beta diversity will be evaluated using permutational multivariate ANOVA based on distance matrices (eg, Bray-Curtis and UniFrac). Visualization will include principal coordinates analysis.

Analyses will follow a 2-level structure, with primary community-level testing and secondary, exploratory taxonomic-level summaries.

Relative abundances of microbial taxa at different taxonomic levels will be summarized descriptively.

Exploratory differential-abundance analyses will be performed using ANCOM-II, a method suitable for sparse compositional data that incorporates its own procedures for controlling false discoveries. Taxonomic-level hypothesis testing will only be performed if community-level analyses indicate meaningful group differences.

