At the same time, the implementation of a fully non–site-bound model presented specific challenges. In the VD group, it was difficult to anticipate the exact timing of delivery and thus ensure timely sample collection at T0 and T1. Participants were encouraged to prepare the sampling kit in advance and bring it to the hospital in their birth bag, but adherence to this instruction was not always possible. Additionally, logistical issues were encountered early in the study due to the use of time-limited digital postage codes. As these codes expired before participants mailed their samples, significant mailing delays occurred. The issue was resolved by switching to traditional postage stamps, which ensured reliable sample dispatch without further complications. Although this did not result in sample loss, it created confusion and required additional follow-up communication. These experiences highlight the need for practical guidance and reliable infrastructure when conducting off-site clinical research.

Recruitment was also affected by varying levels of institutional engagement across study sites. While the home-based design reduced participant burden, it still required initial support from clinical staff to initiate contact or distribute study materials. Staff at one study center demonstrated strong interdisciplinary cooperation, with committed medical professionals actively facilitating participant outreach. This differed significantly in the other study center, where limited personnel resources and skepticism about participants’ willingness to provide samples postpartum led to reluctance in supporting recruitment. This ultimately contributed to the premature closure of enrollment before the initially planned sample size was reached. This limitation in institutional support directly impacted the final sample size, which remained below target and unevenly distributed between the 2 study arms. In addition, several participants had to be excluded during the study due to protocol violations, such as postpartum antibiotic use identified retrospectively through questionnaire data, or delayed sample return beyond the predefined protocol windows. Despite these constraints, the sampling scheme captured three critical time points—before delivery, shortly after birth, and during postpartum recovery—enabling the identification of both acute and long-term changes in microbial composition.

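### The sampling windows are defined by collection, but per-protocol status and the timing outcome are judged by receipt or return; at the two-day T1 window the two clocks give different answers

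*Protocol article*

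**What the plan says.** **Collection clock.** Study Design and Setting and Data Collection and Sample Handling both set the windows as times of collection: T0 from gestational week 32, T1 at 2 to 3 days postpartum, T2 at 90±10 days postpartum. The Abstract lists among the primary outcomes "adherence to sampling windows, and participant retention across follow-up". The Figure 2 legend counts as a deviation "sample collection outside the defined protocol windows and could not be assigned to a valid time point".

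**Receipt or return clock.**
- The same legend, one sentence earlier: "A per-protocol sample was defined as a stool sample received within the prespecified time window and passing quality control".
- Statistical Analysis Plan: timing against the collection windows is evaluated by "calculating time intervals (in d) between the target and actual return dates".
- Outcomes: the primary feasibility indicator is "timeliness of sample returns relative to the predefined sampling windows".
- Discussion, Principal Findings: participants were excluded for reasons that include "delayed sample return beyond the predefined protocol windows".

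**Logistics.** The stabilising tube is meant to keep sample quality reliable "even when samples remained at home for several days before mailing" (Study Design and Setting). Samples then travelled by standard post. The time from sampling to mailing was not recorded for every participant. Data Collection and Sample Handling adds: "No exclusions were made due to transport delays, damage, or temperature fluctuations".

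**The concern.** A stabilised sample represents the gut at the moment of collection. The day postpartum of collection therefore decides whether it is a valid T1 or T2 sample. The day it reaches the coordinating centre depends as well on how long it stayed at home and in the post, and the design allows for both. A rule based on receipt can thus fail a participant who did what the protocol asked.

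Two things are at stake. The first is a primary feasibility outcome. If one interval from target date to return date stands for window adherence, a later team cannot separate mothers who missed the window from parcels that were slow, and these call for different remedies. The second is the analysed set at T1, the time point with the fewest samples. A reader cannot tell which rule produced it.

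**Working it through.** **Inputs from the article.** T1 window: days 2 and 3 (2 calendar days). T2 window: 90±10, that is days 80 to 100 (21 calendar days). Analysed samples in the Figure 2 legend: T0 31, T1 19, T2 21, total 71. Women with at least one sample (Table 1): 31. Women enrolled: 37.

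**Assumed, not in the article.** A lag of L whole days from collection to receipt, shown for 0 to 7, with collection spread evenly over the days of the window.

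**Step 1: reproduce the stated total.** 31 + 19 + 21 = 71, which agrees. No power or sample-size figure is stated that could be reproduced.

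**Step 2: apply the receipt rule to correctly collected samples.** A sample collected on day d passes if d + L is still inside the window. For a window of W days the share passing is (W − L)/W, and zero once L reaches W.

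| Lag L (days) | T1, W = 2 | T2, W = 21 |
|---|---|---|
| 0 | 2/2 = 100% | 21/21 = 100% |
| 1 | 1/2 = 50% | 20/21 = 95% |
| 2 | 0% | 19/21 = 90% |
| 3 | 0% | 18/21 = 86% |
| 7 | 0% | 14/21 = 67% |

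Under a collection-date rule every entry is 100%.

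**Step 3: the opposite error at T1.** A sample collected on day 1, before the window opens, is received on day 2 if L = 1 and on day 3 if L = 2. The receipt rule passes it both times.

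**Step 4: the two legend sentences together.** Take a sample collected on day 3 and received on day 6. It is not per-protocol, because it was received outside the window. On timing it is not a deviation either, because it was collected inside the window. The two definitions leave it unclassified.

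**Step 5: do 19 T1 samples fit a literal receipt rule?** Suppose every woman collected in window, a share s of samples had L = 1, and the rest had L of 2 or more. The pass probability is then s × 0.5.

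| s | Expected of 31 | P(at least 19 of 31) | Expected of 37 | P(at least 19 of 37) |
|---|---|---|---|---|
| 1 | 15.5 | 0.14 | 18.5 | 0.50 |
| 0.75 | 11.6 | 0.006 | 13.9 | 0.06 |
| 0.5 | 7.8 | 0.00002 | 9.3 | 0.0005 |

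Nineteen is plausible only if nearly all samples arrived the day after collection. That sits poorly with standard post and several days at home being allowed. The inference is soft: same-day receipt, mostly day-2 collection or wrongly passed day-1 samples would all raise the expected count.

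**The case against.** **The legend does use collection.** A reader of the per-protocol sentence alone might infer that the study judges timing only by receipt. The following sentence bases exclusion on collection outside the windows, and only where no valid time point could be assigned. This stands: the defect is an inconsistency, and the word received may be loose drafting.

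**No loss of correctly timed samples is shown.** A reader might infer that on-time samples were discarded. The Discussion reports exclusions for late return, but nowhere says that an excluded sample had been collected in window. It also says that the expired postage codes, though they delayed mailing, caused no sample loss. This stands too. Nor does the shortfall of 31 − 19 = 12 women (39%) at T1 measure the problem. It pools all causes, including samples never returned, antimicrobial use and collection out of window. Figure 2, which is not shown, may break it down.

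**The statement on transport delays may concern laboratory acceptance only.** A sample can be accepted for processing and later excluded from analysis. That is a fair reading of Data Collection and Sample Handling, so the conflict with the Discussion is one to clarify, not a proven contradiction.

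**Return timeliness is a proper outcome for a postal study.** A reader might infer that the timing outcome merely measures the post. It also reflects when women collected and when they mailed, and the plan states an interest in logistical barriers. This stands as far as it goes. What remains is that the Abstract presents the outcome as adherence to sampling windows and the Statistical Analysis Plan section ties it to protocol adherence, which a return date alone cannot show.

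**Conclusion.** The concern holds as an inconsistency of definition with a real effect at T1. The windows are collection windows, but the per-protocol definition and the planned timing analysis use receipt or return. Taken literally, the receipt rule fails half of correctly timed T1 samples at a one-day lag and all of them from two days on, and it can admit samples collected too early. At T2 the effect is modest: 5% fail at one day and 33% at seven. These shares rest on assumed lags and on even collection across the window.

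The text does not establish that the receipt rule was the one applied, or that any in-window sample was lost; the 19 analysed T1 samples point, weakly, the other way. The feasibility outcomes are descriptive and the microbiome analyses exploratory, so no confirmatory result is at risk. This should be fixed: it bears on a primary feasibility outcome and possibly on the T1 set, and the analysis was still under way in December 2025.

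**What to change.** 1. Define per-protocol status and window adherence by collection date, expressed as day postpartum for T1 and T2.
2. Report return timeliness, as the lag from collection to receipt, as a separate logistics outcome.
3. Check whether any sample was excluded only for late return although it was collected in window. If so, restore it and say how many.
4. Where the collection date is missing, bound it by the birth date and the postmark or receipt date, flag the sample, and repeat the key summaries without flagged samples.
5. Reconcile the wording in Data Collection and Sample Handling, Outcomes, Statistical Analysis Plan, the Figure 2 legend and the Discussion. State whether the sentence on transport delays refers to laboratory acceptance or to analysis.

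**Cost.** One timing variable is re-derived from records that the collection-based deviation rule already presupposes; no new sampling is needed. The downside is that some collection dates may be missing: the article does not list the date among the questionnaire items, and the sampling-to-mailing time is incomplete. For those samples the bounds may be wide. At T2 the birth date is little help as a lower bound, so some will stay flagged.

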Interested individuals were first approached by clinical staff and subsequently contacted by the study coordinator. Informed consent was obtained remotely in a 2-step process. Following an initial telephone-based eligibility screening and verbal explanation, participants confirmed their consent in writing by mailing back the signed documents together with their first stool sample and completed questionnaire.

Assignment to study groups was based on the actual mode of delivery. Women initially recruited for the control group who ultimately required CS for medical reasons were reallocated to the intervention group. Recruitment concluded after inclusion of 25 women in the CS group and 12 in the vaginal birth group, without reaching the originally planned sample size.

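### The Figure 2 legend counts two women as VD at T0 but as CS at T1 and T2, against the article's own rule of grouping by actual delivery mode

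*Protocol article*

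**What the plan says.** The protocol article defines the groups in four places.

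- **Eligibility and Recruitment:** "Assignment to study groups was based on the actual mode of delivery". On switches it adds: "Women initially recruited for the control group who ultimately required CS for medical reasons were reallocated to the intervention group".
- **Data Collection and Sample Handling:** "Final group assignment (CS vs VD) was based retrospectively on the actual mode of delivery at birth". Neither Methods section makes an exception for T0.
- **Results, Table 1:** the 31 women with at least one stool sample are split into 20 CS and 11 VD. The delivery-mode rows are 100% CS in one column and 100% VD in the other.
- **Figure 2 legend:** "Two women, who were initially allocated to the vaginal delivery group, delivered by CS and were therefore analyzed in the CS group". The same sentence continues: "these women are counted under vaginal delivery at baseline (T0) and under CS at follow-up (T1 and T2". The next sentence says: "Numbers reported per group reflect participants analyzed at each time point", with totals "T0 (n=31), T1 (n=19), T2 (n=21), and final analysis (N=71".

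The Outcomes and Statistical Analysis Plan sections call for CS versus VD comparisons at each of T0, T1 and T2, and for longitudinal description both within participants and within groups. The Microbiome Analysis and Bioinformatics Pipeline section evaluates longitudinal change through within-individual distances.

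**The concern.** T0 is the sample taken before delivery and before any prophylaxis. In a non-randomized comparison it is the only microbiome evidence on whether the two groups were alike beforehand. For that purpose, a woman's T0 sample needs the same group label as her later samples.

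The legend gives two women one label at T0 and another at follow-up, and describes the resulting counts as analysis counts. If the analysis follows the legend, two things go wrong. The T0 comparison of CS with VD is diluted, because some samples labelled VD belong to women who delivered by CS. And any unpaired group summary across time compares groups whose membership changes between T0 and T1, so a relabelling can appear as a change in the microbiome or mask one.

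**Working it through.** **Inputs.** Two women switch label (Figure 2 legend). Sample counts are 31, 19 and 21 at T0, T1 and T2 (same legend). Table 1 has 20 CS and 11 VD.

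**Reproducing the article's figures.** 31 + 19 + 21 = 71, the stated final total. 20 + 11 = 31, the stated Table 1 total. Both agree.

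**Same women.** Table 1 covers everyone with at least one sample (31), and T0 has 31 women. With one T0 sample per woman, the T0 set and the Table 1 set are therefore the same women.

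**T0 split under the legend's rule.** Table 1 is by actual delivery mode, so both switchers are among its 20 CS women. Moving them to VD at T0 gives:

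| Labelling | CS at T0 | VD at T0 | Total |
|---|---|---|---|
| Actual delivery mode (Methods, Table 1) | 20 | 11 | 31 |
| Figure 2 legend as written | 20 − 2 = 18 | 11 + 2 = 13 | 31 |

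- Share of the VD baseline that delivered by CS: 2/13 = 15.4%.
- Share of CS women missing from the CS baseline: 2/20 = 10%.

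**Effect on the T0 comparison.** Let μC and μV be the true T0 means of women who deliver by CS and by VD, and assume that the two switchers resemble the other CS women. The labelled VD mean is (11·μV + 2·μC)/13 and the labelled CS mean stays μC. The labelled difference is

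μC − (11·μV + 2·μC)/13 = (11/13)·(μC − μV) = 0.846·(μC − μV).

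About 85% of a true T0 mean difference survives. This is exact for a mean. For rank tests and distance-based tests it shows the direction only.

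**Effect on unpaired within-group summaries.** Under the legend the VD group contains the two women at T0 and not at follow-up. Even with no biological change in anyone, and everyone returning samples, the VD mean would move by (2/13)·(μV − μC) between T0 and follow-up. If the groups do not differ at T0 there is no systematic shift, only extra noise from changing membership.

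**What is not affected.** A woman's own T0–T1 or T0–T2 distance does not depend on any label. It only needs one group when the distances are compared between groups, and the Methods rule supplies it (CS). At T1 and T2 the legend already labels both women CS. The totals 31, 19, 21 and 71 are the same under either labelling.

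**The case against.** The best defence is that the legend only describes flowchart placement: the women are drawn in the VD stream before birth and in the CS stream after it. There is support for this. Every other statement in the article groups by actual mode, the legend itself says both women were analyzed as CS, and the Statistical Analysis Plan section contains no split-label rule. The per-group T0 counts are in a figure not available here, so 18/13 is derived and not read. It is therefore not established that the analysis files carry split labels. That stands.

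It does not remove the problem. The sentence after the split label says the per-group numbers are those analyzed, which does not fit a purely graphical reading. If only placement was meant, the legend misdescribes its own counts and still needs correcting.

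A reader might go further than the article supports in three ways:

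- **Baseline contaminated by the exposure.** T0 precedes delivery and prophylaxis, so neither group has had the study exposure. The fault is misclassified membership.
- **All longitudinal results compromised.** Within-individual distances are sound if each pair carries the actual mode. The hypotheses on alpha diversity and *C. difficile* compare groups at T1, and the third concerns resolution by T2. The legend labels both women CS at both times.
- **Table 1 might use the T0 labels**, giving 22 CS / 9 VD by actual delivery and a misclassified share of 2/11 = 18%. Table 1's delivery-mode rows rule this out.

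**Conclusion.** The inconsistency is real: the Figure 2 legend contradicts the two Methods statements on group assignment, Table 1, and its own statement that the women were analyzed as CS. If the legend is followed, 2 of 13 VD baseline samples (15%) come from women who delivered by CS. A true T0 mean difference would be reduced to about 85% of its size, and unpaired group summaries from T0 to follow-up would compare different sets of women.

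The size rests on three assumptions: Table 1 is by actual delivery mode, as its rows show; the legend means what it says about analysis counts; and, for the 85%, the two women resemble the other CS women at T0.

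This is something that should be fixed, but it does not undermine the study. The microbiome outcomes are exploratory with no confirmatory test, and the overall feasibility totals do not change. Only feasibility figures reported by delivery group, such as return or retention rates, would have shifting denominators. Exploratory status limits what may be concluded, but it does not justify two exposure labels for one woman.

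**What to change.** 1. State in the Statistical Analysis Plan section that each woman has one group label, her actual delivery mode, and that it applies at T0, T1 and T2 to all microbiome analyses, to between-group comparisons of paired distances, and to all by-group counts.
2. Correct the Figure 2 legend, and make the T0 counts 20 CS / 11 VD to match Table 1. Show the two switches only as a flowchart footnote.
3. Check the labels in the analysis metadata. If the two T0 records are labelled VD, change them and rerun the T0 comparison and the within-group summaries. If they already read CS, only the legend and the T0 counts need to change.

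A sensitivity analysis without these two women is optional.

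The cost is small: one sentence, a corrected figure and legend, and at most two relabelled records with a rerun of scripts. The Results section reports the analyses as still ongoing in December 2025 and gives no microbiome result, so no microbiome finding in the article has to be withdrawn.
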